### RECALL trial: Treatment allocation, intervention, and blinding

After inclusion in the trial, randomization is organized with a two by two Williams design (29). Block randomization is performed by the pharmacy department of the Amsterdam University Medical Center—location VUmc, with stratification for each site. Patients are randomly assigned to either the rivastigmine-followed-by-placebo group, or the placebo-followed-by-rivastigmine group. Each treatment arm lasts for four consecutive ECT sessions (Figure 1). Except for the unblinded nurse or research assistant (i.e., nurse or research assistant who is not involved in other parts of the study, nor in clinical practice, but only applies the patches), all other study members are blinded. “Trial treatment randomization lists” with codes are provided by an independent pharmacist and will only be available for the unblinded nurse or research assistant who applies the patches. Rivastigmine patches delivering 4.6 mg/24 h (Hexal AG, Holzkirchen, Germany) and Hansaplast® placebo patches (of similar size) are labeled in accordance with EU GMP annex 13 regulations and supplied to the sites. To improve and monitor adherence to the trial protocol, drug accountability lists are filled in. The Tmax of rivastigmine patches is 10–16 h, therefore the application of the rivastigmine (and placebo) patches is done the evening prior to ECT. The patch is removed after 24 h. As previously mentioned, during the trial, co-medication is allowed and there are no restrictions to clinical care as usual. As specified in the exclusion criteria however, patients with adjustments in antipsychotic medication or in electrode placement, are excluded from the trial. Benzodiazepines are allowed (e.g., in cases of profound agitation or insomnia). All changes in medications during the trial are registered after every ECT-session. Prior to each ECT-session, side-effects of rivastigmine are assessed, and in case of serious side-effects (e.g., gastrointestinal adverse reactions such as severe nausea), the participation in the trial will be stopped and rivastigmine discontinued. In case of persistent side-effect after discontinuation, the clinician will treat the patient according to the clinical picture (e.g., anti-emetics in case of nausea).

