### Study design and research setting

The RECALL study combines a multicenter, prospective cohort study on older patients with depression who are referred for ECT to study the broad palette of cognitive side-effects (and their determinants), with an embedded cross-over trial to examine rivastigmine as a treatment option for patients with inter-ictal delirium (see Figure 1 for a schematic overview of the RECALL study). The trial is designed as a randomized, double blind, placebo-controlled, cross-over trial. Patients are recruited at four mental healthcare institutes; (1) GGZ inGeest (partner-institution of Amsterdam University Medical Center, formerly VU University Medical Center), Amsterdam, The Netherlands, (2) Parnassia Psychiatric Institute, The Hague, The Netherlands, (3) OLVG-West, Amsterdam, The Netherlands, and (4) UPC KU Leuven, Leuven, Belgium. GGZ InGeest, and Parnassia Psychiatric Institute are general mental healthcare institutes; OLVG West is a general hospital with a psychiatric ward, and UPC KU Leuven is an academic hospital.

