#### Primary outcome measure

During the trial, the effect of rivastigmine on inter-ictal delirium is examined through the Delirium Rating Scale-Revised-98 (DRS-R-98) (30). It was demonstrated that the DRS-R-98 is sensitive, specific, reliable, and easy to use for the assessment of severity of a delirium (30). We will compare delta-scores of the DRS-R-98 computed over the period of rivastigmine-use and placebo (T3-T0 and T6-T3, depending on whether the patients start with rivastigmine or placebo). This is assessed by a trained, blinded research nurse once weekly.

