
Furthermore, in order to investigate the safety and effect of rivastigmine on ECT-parameters and anesthesia, we measure blood pressure, peak heart rate, seizure length (EEG and motor duration in seconds), postictal suppression index (in %) and seizure threshold. Apart from the postictal suppression index and seizure length measured by the Thymatron IV (unavailable at sites with the spECTrum), all variables are recorded by a blinded anesthesiologist. Next, side-effects of rivastigmine are evaluated twice weekly (by a research assistant) using a four-point side-effects scale with the five most common side-effects of rivastigmine (nausea, vomiting, diarrhea, abdominal pain, allergic skin reaction), and an open question for additional side-effects.

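### The placebo plaster is described as matching the rivastigmine patch in size, with no other match or concealment stated, so the double blind is at risk while the patch is worn; the primary ratings are exposed only indirectly.

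*Protocol article*

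**What the plan says.** Under *Study design and research setting* the article states: "The trial is designed as a randomized, double blind, placebo-controlled, cross-over trial". The section on treatment allocation, intervention and blinding gives the means:

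- The active product is "Rivastigmine patches delivering 4.6 mg/24 h (Hexal AG, Holzkirchen, Germany"; the comparator is "Hansaplast® placebo patches (of similar size". Size is the only matching attribute given.
- One person is unblinded: a "nurse or research assistant who is not involved in other parts of the study, nor in clinical practice, but only applies the patches". Apart from that person, "all other study members are blinded".
- Active and placebo patches are applied on the evening before ECT. "The patch is removed after 24 h"; who removes it is not stated.
- Code lists go only to the applier, and the patches carry clinical-trial labelling.

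The primary outcome is the change in DRS-R-98, T3 minus T0 and T6 minus T3. On the rater, *Primary outcome measure* says: "This is assessed by a trained, blinded research nurse once weekly". Table 1 also schedules the DRS-R-98 at T1, T2, T4 and T5, within 90 minutes after ECT. The five listed side-effect items are "nausea, vomiting, diarrhea, abdominal pain, allergic skin reaction".

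**The concern.** A branded wound plaster and a drug patch from another manufacturer are two different products. A match in size does not make them indistinguishable. The dedicated applier, who is kept out of every other study task, would be a sensible arrangement for patches that can be told apart. It protects the code list and the moment of application, but not the hours during which the product is on the skin.

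The cross-over sharpens the problem in two ways. Each patient wears both products in turn and can compare them. Any expectation tied to the visible product also follows treatment in both sequences, so using patients as their own controls does not remove it.

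At stake are ratings that depend on an observer or on the patient: DRS-R-98, RASS, reorientation time and the side-effects scale.

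**Working it through.** The plan gives no figure on this point, so there is none to reproduce. The check sets wear time against the assessment schedule.

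**1. Is the patch on at the post-ECT ratings?** From the article: on the evening before ECT, off after 24 h, post-ECT ratings within 90 minutes. Clock times are not given. I assume application between 18:00 and 22:00 and ECT between 08:00 and 14:00.

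- Hours worn at ECT = (24 − application time) + ECT time. Shortest: (24 − 22) + 8 = 10 h. Longest: (24 − 18) + 14 = 20 h.
- At the end of the 90-minute window: 10 + 1.5 = 11.5 h to 20 + 1.5 = 21.5 h.

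Both are below 24 h, so the patch is worn during ECT and throughout the windows at T1, T2, T4 and T5.

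**2. Is it on at the primary ratings?** Table 1 places T3 and T6 on the day after the second and fourth ECT. At an assumed 09:00 that day, hours since removal = (24 − application time) + 9, which runs from (24 − 22) + 9 = 11 h to (24 − 18) + 9 = 15 h. The patch is off.

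**3. Who can see it, and what do they supply?**

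| Person | When the patch is on | Data affected |
|---|---|---|
| Patient | Every wear period, both products | Side-effect answers; own behaviour and expectation |
| Post-ECT rater | T1, T2, T4, T5 | DRS-R-98, RASS, reorientation time, side-effects |
| Anesthesiologist, described as blinded | During ECT | Blood pressure, peak heart rate, seizure measures |

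**4. What reaches the primary outcome?** Two indirect routes remain: a patient who has recognised the product, and a rater who saw it after the preceding ECT. The article uses the title of research nurse both for the weekly DRS-R-98 and for the reorientation assessment after ECT. It does not say whether this is the same individual, and it does not separate the two tasks.

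**5. Can the bias be sized?** No. It would need the share of ratings affected and the shift in points, and the article gives neither. Even a known shift would not enter one for one, because T3 closes the first period and opens the second. Suppose ratings that end a rivastigmine period are lowered by *b* and all others are unaffected:

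- Rivastigmine first: rivastigmine delta −*b*, placebo delta +*b*, difference −2*b*.
- Placebo first: placebo delta 0, rivastigmine delta −*b*, difference −*b*.

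With equal sequence sizes the average is (−2*b* − *b*)/2 = −1.5*b*. This shows how such a shift would propagate. It is not evidence that *b* differs from zero.

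**The case against.** The strongest reply is that this is a condensed article. It says the plasters are similar in size; it does not say that size is the only thing matched, that the products look different, or that they are visible. Body site and covering may be laid down in the full protocol or pharmacy instructions, which are not shown. This stands as a limit: different appearance is inferred from the two named products, and a concealment procedure may exist. It does not remove the point, because the article itself names the comparator, gives one matching attribute and asserts that everyone else is blinded. The first two do not support the third.

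Several further objections are right:

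- A reader might infer that unblinding adds directly to the primary rivastigmine effect. The schedule does not support that, since no patch is worn at T3 or T6.
- A reader might put a size on it. Assuming 30–80% of ratings affected and a shift of 1–2 points gives 0.3 × 1 = 0.3 to 0.8 × 2 = 1.6 points, or 7.5% to 40% of the 4-point target. Both inputs are assumptions, and the product is not derived for the planned delta scores. It should not be quoted as a finding.
- The ECT variables are largely instrument readings, with little room for expectation.
- The article does not say that the skin-reaction item involves inspecting the site.
- Real safeguards exist: a separate applier, restricted code lists, and emergency envelopes stored apart from the patches.

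**Conclusion.** The point holds as a risk to blinding, not as a demonstrated failure. As described, the comparator does not secure the blind that the article claims for patients, post-ECT raters and ECT staff. Exposure is direct at T1, T2, T4 and T5 and for patient-reported side-effects. It is only indirect at T3 and T6, through the patient's knowledge or a rater's earlier sight of the patch. For the anesthesiologist's recordings the practical consequence is small.

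The conclusion rests on two things: the inference that the two products can be told apart, and the absence of any stated concealment in this article. The clock times used in the check are assumptions, but the ordering holds across the range shown. The size of any bias cannot be derived from the documents. No sample-size or significance figure in the plan depends on this point.

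**What to change.** - Have the unblinded person who already applies the patches cover both products with an identical opaque dressing compatible with the patch's labelled use, or otherwise keep them out of sight. The same person should also remove them.
- Instruct the DRS-R-98, RASS and reorientation raters not to view the site.
- Where the skin-reaction item needs the site to be looked at, have this done by someone who does not rate those outcomes. It should not fall to the unblinded applier, which would put a rivastigmine side-effect outcome in the hands of the one person who knows the allocation.
- Ask the patient and the DRS-R-98 rater for a treatment guess once, after T6, and report it. A guess after T3 would invite speculation before the second primary rating.
- If concealment of this kind is already in place, say so. If the patches cannot be concealed, qualify the double-blind claim.

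The cost is the dressings, a short work instruction, one extra task for the applier, an independent site check where needed, and one question each for patient and rater. The cover may irritate the skin, equally in both periods. Sample size and visit schedule are unaffected.

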### RECALL trial: (Emergency) unblinding procedure

Unblinding will take place after ending the treatment period by the research nurse. Emergency unblinding may occur on an individual basis for safety reasons—such as the occurrence of a (Serious) Adverse Event [(S)AE] or Suspected Unexpected Serious Adverse Reaction (SUSAR). The medical team will contact the local investigator, through which the decision to unblind will be made. For emergency unblinding, envelopes are available at the medication storage room at the in-patients' ward, kept separately from the patches. The sealed envelope can be opened by anyone on the clinical team. The reason and time of unblinding will be documented in the study files.

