### Outcome measures

Table 1 shows a full summary of patient characteristics and outcome measures, including the time of collection.

**Table 1 T1:** Collection of patient characteristics and outcome measures in the RECALL trial and cohort.

	**Baseline**	**Regular care**		**Trial**							**Regular care in cohort**		
		**in cohort**									**after finishing the trial**		
	**Baseline**	**Max 90 minutes after ECT**	**Once a week during ECT** ^∧^	**Day before first ECT**	**Max 90 minutes after first ECT**	**Max 90 minutes after 2**^nd^ **ECT**	**Day after 2**^nd^ **ECT**^∧^	**Max 90 minutes after 3**^rd^ **ECT**	**Max 90 minutes after 4**^th^ **ECT**	**Day after 4**^th^ **ECT**^∧^	**Max 90 minutes after ECT**	**Once a week during ECT** ^∧^	**1 week after stop ECT**
Time	Ta	Tb		T0	T1	T2	T3	T4	T5	T6	Tb		
Socio-demographics	X												
*General clinical-demographics*													
Medical history	X												
Substance use	X												
Medication use	X	X		X	X	X		X	X	X	X		X
ATHF	X												
BMI	X												
Waist circumference	X												
Blood pressure	X												
*Physical activity and frailty*													
Frailty index	X												X
SPPB	X												X
Physical activity*	X												
Vision and hearing ability	X												
*Depression related clinical characteristics*													
BAI^a^	X												
GDS^a^	X												
AES^a^	X			X			X			X			X
MADRS^a^	X		X				X			X		X	X
CORE	X		X				X			X		X	X
*Neurocognitive characteristics*													
Battery of neuropsychological tests**	X												X
Self reported cognitive decline	X												X
IQCODE	X												X
(f)MRI	X												
EEG	X												
*Laboratory characteristics*													
Blood / urine sample	X			X									X
*Primary outcome measure*													
DRS-R-98				X	X	X	X	X	X	X			
*Secondary outcome measures*													
MMSE	X		X				X			X		X	X
Letter fluency	X			X			X			X			X
Clock Drawing Test	X			X			X			X			X
Reorientation time		X			X	X		X	X		X		
RASS		X			X	X		X	X		X		
CAM		X	X										
ECT characteristics		X			X	X		X	X		X		
Rivastigmine side-effects				X	X	X		X	X	X			

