*ATHF, Antidepressant Treatment History Form; BMI, Body Mass Index; SPPB, Short Physical Performance Battery; BAI, Beck Anxiety Inventory; GDS, Geriatric Depression Scale; AES, Apathy Evaluation Scale; MADRS, Montgomery Åsberg Depression Scale; IQCODE, Informant Questionnaire on Cognitive Decline in the Elderly; DRS-R-98, Delirium Rating Scale-Revised-98; MMSE, Mini-Mental State Examination; RASS, Richmond Agitation Sedation Scale; CAM, Confusion Assessment Method*.

∧ *The day of measurement is Wednesday, as ECT is done twice weekly*.

* *Physical activity includes assessment of mobility, International Physical Activity Questionnaire (IPAQ), and self-reported activities of daily living (ADL)*.

** *Stroop Color Word Test, 15-Words Test or Auditory Verbal Learning Test, Trail making Test, Kopelman Autobiographic Memory Interview, and Visual Association Test*.

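### Routine unblinding is tied to an undefined end of treatment, not to the last primary rating or database lock, so codes can be read as opening before T6 and patient by patient

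*Protocol article*

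**What the plan says.** The unblinding section gives the routine rule in one sentence: "Unblinding will take place after ending the treatment period by the research nurse". The rest of that section covers emergency unblinding, and only there does it speak of unblinding individual patients.

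Other sections bear on what the rule means:

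- **Patch timing** (treatment allocation, intervention and blinding section). Application of the "patches is done the evening prior to ECT", and "The patch is removed after 24 h".
- **Last primary rating** (Table 1). The DRS-R-98 is marked at T0 to T6, and T6 is headed "Day after 4^th^ ECT". A footnote to T3 and T6 adds: "The day of measurement is Wednesday, as ECT is done twice weekly".
- **Primary contrast** (primary outcome section). The deltas are "T3-T0 and T6-T3, depending on whether the patients start with rivastigmine or placebo", so T6 enters every patient's second-period delta. On the rater: "This is assessed by a trained, blinded research nurse once weekly".
- **Allocation** (treatment allocation section). "Block randomization is performed by the pharmacy department", stratified by site. The lists are held only by the unblinded nurse or assistant, who applies patches and has no other part in the study. All other study members are blinded.
- **Period length.** The data analysis section gives two ECT sessions and 7 days per treatment. The treatment allocation section gives four sessions per treatment arm.

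**The concern.** The DRS-R-98 is rated by an observer, and the double-blind claim on the primary outcome depends on that observer not knowing the sequence until the last rating is recorded. A rule that starts from the end of treatment, without defining it, leaves the site to decide whether that means the last patch, the T6 visit or the end of the trial.

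The second risk is allocation concealment. If codes are opened as each patient finishes, staff at a site see the earlier entries of the current block and can work out or guess some later ones. Local judgement affects both entry and retention: the clinician decides whether other causes of delirium need to be excluded, and a change of electrode placement or antipsychotic dose makes a patient a drop-out.

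**Working it through.** The plan gives no figure on this point to reproduce. I made three checks.

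**1. Order of events around T6.** The last patch goes on the evening before the 4th trial ECT and comes off 24 h later, on the evening of the ECT day. T6 is the next day. Clock times are not given. Assuming application at 18:00 to 22:00 and rating at 09:00 to 17:00:

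- shortest gap: off at 22:00, rated at 09:00 = 11 h
- longest gap: off at 18:00, rated at 17:00 = 23 h

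Three readings of the end of treatment then follow:

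| Reading | Basis | Code may open |
|---|---|---|
| Last patch removed | Patch timing | 11 to 23 h before T6 |
| End of the second analysis period | Primary outcome and data analysis sections | At or after T6 |
| Four sessions per treatment | Treatment allocation section, if arm means one treatment | After the T6 shown in Table 1 |

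The data analysis section uses arm for a sequence. In that sense, four sessions would cover both treatments and agree with Table 1. The article does not say which sense applies in the allocation section.

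**2. What an unblinded T6 would do to the contrast.** The within-patient contrast is (T6 − T3) − (T3 − T0) = T6 − 2·T3 + T0, with the sign reversed for the other sequence. T6 carries 1 of 4 units of absolute weight, but an error in it passes through undiluted. Suppose a rater who knows the sequence scores T6 b points lower after rivastigmine and b points higher after placebo. The rivastigmine-minus-placebo contrast then shifts by −b in both sequences. For illustration, b = 1 is 1/4 of the 4-point reduction used in the sample size section.

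**3. Predictability under patient-by-patient opening.** Block size is not stated, so I take 2, 4, 6 and 8 as assumptions. In a balanced block of size 2m, an allocation is fully determined once the other sequence is used up. The expected number of such allocations is 2m/(m+1), so their share is 1/(m+1). Check for a block of 4: the last is always determined and the third with probability 1/3, so (1 + 1/3)/4 = 33%. Enumerating all balanced blocks gives the same shares, and also the success rate of a best guess (50% means no information).

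| Assumed block | Share determined | Of 38 patients | Best-guess success |
|---|---|---|---|
| 2 | 1/2 = 50% | 19.0 | 75% |
| 4 | 1/3 = 33% | 12.7 | 71% |
| 6 | 1/4 = 25% | 9.5 | 68% |
| 8 | 1/5 = 20% | 7.6 | 67% |

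These are upper bounds. They need every earlier patient in the block to be unblinded already and the block size to be known to staff. The counts of 38 also assume complete blocks, which four sites may not fill. If codes stay closed until the last T6 and database lock, routine unblinding determines none and the best-guess rate is 50%.

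**The case against.** A reader might infer that the plan unblinds before T6, that the rater does the unblinding, and that later sequences are revealed. The documents support none of these as stated fact.

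- **Timing.** Where the article defines a period, it does so by assessment: the deltas run to T3 and T6, and the analysis counts 7 days per treatment. Table 1 also places T6 within the trial. On that usage the treatment period ends at T6. This stands, and opening before T6 is only one reading.
- **Who unblinds.** The allocation section separates the list-holding nurse from all other staff, and the primary outcome section requires a blinded rater. A shared job title is not a shared person. This stands too. But if the nurse meant is the list-holder, that person already knows the codes, so unblinding must mean telling someone else. The rule does not say whom, and it does not exclude the rater.
- **Patient-by-patient opening.** Individual unblinding is mentioned only for emergencies, which may imply that routine unblinding is not individual. The rule does not say so, however, and treatment ends patient by patient.
- **Block size.** A condensed article may leave it out, and its absence is not criticised here. It does mean that the percentages are assumptions.
- **Selection bias.** Consent for the trial is taken at cohort entry, entry is triggered by the CAM or an MMSE drop of at least 4, and every patient is assigned both treatments. This limits the harm well below that in a parallel-group trial. It does not remove it: clinical judgement about other causes of delirium and about trial drop-out remains, and the two sequence groups still need to be comparable when the course of delirium changes over time.

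**Conclusion.** The concern holds as a badly fixed rule, not as a demonstrated breach of blinding. No reading of the sentence ties the opening of codes to data lock, and none bars the DRS-R-98 rater from learning them. The wording can be read as allowing opening in the 11 to 23 h (assumed clock times) before T6. It can also be read as allowing opening patient by patient, with at most 20% to 50% of sequences determined in advance for assumed blocks of 8 down to 2. The true exposure depends on how sites apply the rule and on a block size that is not given; it could be nil. The rule should still be changed, because the primary outcome is an observer rating in a small trial and the repair is almost free.

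**What to change.** Replace the routine unblinding sentence with a rule to this effect:

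> Apart from emergency unblinding, treatment codes stay closed to all raters, recruiters, research nurses, and treating clinicians who recruit or judge eligibility, until the last patient's T6 rating is complete and the database is locked. The DRS-R-98 rater neither performs nor receives unblinding.

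The unblinded nurse or assistant who applies patches keeps the access already described, and emergency unblinding is unchanged. Treating clinicians need to be covered because the treating physician may inform candidates about the study, and the clinician judges whether other causes of delirium need excluding. Telling them the sequence after each patient finishes would reopen the leak within blocks.

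Reconcile the two-session and four-session descriptions (treatment allocation section, Table 1, data analysis section) so that the end of a treatment period has one meaning.

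The cost is two sentences and one clarified term, with no change to sample size or visits. The small downside is that the team and patients learn the sequences later.
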